**Study design:**

This will be a randomised multi-centric clinical trial

**Treatment Regimens:**

Patients found eligible for admission to the study will be randomly allocated to the following regimens:

Regimen 1:

2 MHRZ thrice weekly/ 2 MHR thrice weekly: moxifloxacin, isoniazid, rifampicin and pyrazinamide thrice-weekly for 2 months followed by moxifloxacin, isoniazid and rifampicin thrice-weekly for 2 months. (Duration 4 months).

Regimen 2:

2 GHRZ thrice weekly/ 2 GHR thrice weekly: gatifloxacin, isoniazid, rifampicin and pyrazinamide thrice-weekly for 2 months followed by gatifloxacin, isoniazid and rifampicin thrice-weekly for 2 months. (Duration 4 months).

Regimen 3:

2 EHRZ thrice weekly/ 4 HR thrice weekly: ethambutol, isoniazid, rifampicin and pyrazinamide thrice-weekly for 2 months followed by isoniazid and rifampicin thrice-weekly for 4 months. (Duration 6 months)

Patients allocated to regimens 1 and 2 will receive 27 doses each in the intensive and continuation phase respectively. Missed doses will be compensated up to maximum of 15 days after the scheduled 2nd and 4th monthly examinations.

Patients allocated to regimen 3 will receive 27 doses in the intensive phase and 54 doses in the continuation phase. Missed doses will be compensated up to a maximum of 15 days after the scheduled 2nd and 6th monthly examinations respectively.

Every dose of treatment will be given under direct observation. Patients who default for treatment will be visited at home by a Health Visitor, Social Worker and Doctor sequentially, and motivated to attend for treatment.

Dosage of drugs in mg:

Isoniazid - 600; rifampicin - 450; pyrazinamide - 1500; ethambutol - 1200; gatifloxacin - 400; moxifloxacin – 400

Patients weighing 60 kg or more will receive rifampicin 600 mg

**Sample size:**

Applying an equivalence design and

assuming that the efficacy of the control regimen (Regimen 3) will be 95% (0.95) in patients with drug susceptible disease, taking into account both failures at the end of treatment and relapse over 24 months,

Type I error to be 5% (0.05, 1 tail) Z = 1.64 and

Type II error to be 10% (0.1) Z = 1.28 and

the definition of equivalence as 5% (0.05),

the sample size required for each regimen was calculated to be 2 (0.95 x 0.05) (1.64 + 1.28)2/(0.05)2 = 323.

Sample size for 3 regimens = 3 x 323 = 969

Loss in follow-up over 24 months is expected to be 10% (0.01)

Proportion of patients with drug resistant tuberculosis at intake is expected to be 10% (0.01)

The required sample size for the trial will therefore be 969/ (0.9 x 0.9) = 1196 or approximately 1200 patients

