**27th December 2003**

Following review of the interim findings of the above study, and recommendations by the DSMB on 14th October 2006, and by the Ethics Committee Meeting of 4th November 2006, and the decision taken by the Clinic Doctors Meeting of 13th November 2006, the above protocol is being amended as follows:

Page 5, Regimen 1:

For the patients admitted to 2MHRZ3/2MHR3 regimen, moxifloxacin will be terminated from 15.11.06 and the treatment will be modified as follows:

In the Intensive Phase, patients will receive EHRZ3 instead of MHRZ3.

In the continuation phase patients will receive HR3 instead of MHR3.

At the end of 4 months HR3 will be extended for 2 more months.

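### The 2006 amendment stops moxifloxacin but leaves the three-regimen sample size in place, so the stated size and 90% power no longer hold for Regimen 1 versus Regimen 3

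*Supplement*

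**What the plan says.** The protocol's Sample size section takes a control efficacy of 95% in drug-susceptible patients, a one-tailed 5% type I error, a 10% type II error and a 5-point margin, and arrives at 323 per regimen. It then multiplies by three: "Sample size for 3 regimens = 3 x 323 = 969". Allowing 10% for loss to follow-up and 10% for drug resistance at intake, it concludes: "The required sample size for the trial will therefore be 969/ (0.9 x 0.9) = 1196 or approximately 1200 patients".

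The 2006 amendment, made after interim findings and recommendations of the DSMB and the Ethics Committee, states that for patients admitted to Regimen 1 "moxifloxacin will be terminated from 15.11.06 and the treatment will be modified as follows". It covers both phases. For the first: "In the Intensive Phase, patients will receive EHRZ3 instead of MHRZ3". In the continuation phase moxifloxacin is dropped from the combination, and that phase is extended by two months. The only place it amends is the description of Regimen 1. The 2005 amendment does not touch the sample size either.

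**The concern.** The sample size is built on three regimens that can each supply 323 evaluable patients treated as described under Treatment Regimens. From 15.11.06 that is no longer possible for Regimen 1. Anyone still in its intensive or continuation phase leaves the moxifloxacin combination before completing it. Anyone allocated to it afterwards never receives moxifloxacin, and gets the same drugs for the same length as Regimen 3.

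Two things are at stake. The plan still carries a 90% power figure for a moxifloxacin comparison whose size is fixed at whatever had been reached by that date, so a wide interval could be read as the result of a fully powered comparison. And the trial has no current recruitment target, because the total of about 1200 is the sum over three recruiting arms.

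**Working it through.** **Inputs, all from the Sample size section.** Control efficacy 0.95 ("assuming that the efficacy of the control regimen (Regimen 3) will be 95% (0.95) in patients with drug susceptible disease"); one-sided alpha 0.05 ("Type I error to be 5% (0.05, 1 tail) Z = 1.64 and"); power 90% ("Type II error to be 10% (0.1) Z = 1.28 and"); margin 0.05; 10% loss to follow-up and 10% drug resistance, applied as 0.9 x 0.9 = 0.81.

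**Step 1: the plan's own figures.** With a true difference of zero,

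n per regimen = 2 p(1 - p)(z_alpha + z_beta)² / margin² = 2 x 0.0475 x (1.64 + 1.28)² / 0.05² = 324.0.

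The plan states 323; unrounded z values give 325.4. The difference is immaterial. Then 3 x 323 = 969 and 969/0.81 = 1196.3, matching the stated 1196.

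**Step 2: Regimen 2 versus 3.** The formula has no multiplicity term and treats each regimen separately, so this comparison does not depend on Regimen 1. Using

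power = Phi(0.05/SE - 1.645), SE = sqrt(0.0475/n1 + 0.0475/n3),

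323 per arm gives SE = 0.0171 and power of 89.8%. The stated 90% stands.

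**Step 3: target if only Regimens 2 and 3 still recruit.** 2 x 323 = 646 evaluable; 646/0.81 = 797.5, so 798 enrolled, or about 400 per arm. Patients already entered in Regimen 1 come on top.

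**Step 4: Regimen 1 versus 3.** The number in Regimen 1 at 15.11.06 is not given. The shares below are assumptions. The two power columns differ in the controls used: only those recruited concurrently (taken as equal in number to Regimen 1), or all 323 planned.

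| Share of 323 reached | Evaluable in Regimen 1 | Power, concurrent controls | Power, 323 controls |
|---|---|---|---|
| 25% | 81 | 43% | 58% |
| 50% | 162 | 66% | 77% |
| 75% | 242 | 81% | 85% |
| 90% | 291 | 87% | 88% |
| 100% | 323 | 90% | 90% |

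Worked example for the 50% row. With concurrent controls, SE = sqrt(2 x 0.0475/162) = 0.0242, 0.05/0.0242 = 2.065, and Phi(2.065 - 1.645) = 0.66. With 323 controls, SE = sqrt(0.0475/162 + 0.0475/323) = 0.0210, 0.05/SE = 2.383 before rounding SE, and Phi(2.383 - 1.645) = 0.77.

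For precision, the 90% interval half-width with concurrent controls is 1.645 x SE: about 5.6, 4.0, 3.3 and 3.0 points at the four shares below 100%, against a 5-point margin.

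**The case against.** The strongest reply has four parts.

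- *The calculation is correct and one comparison is untouched.* This stands. A reader might infer that the sample size is miscalculated, or that the plan's size and power fail for the whole trial. The documents support neither: 969 and 1196 reproduce, 323 agrees to within rounding, and Regimen 2 versus 3 is unaffected.
- *The shortfall is not documented.* Regimen 1 could have been close to its target on 15.11.06, and the loss of power would then be two or three points. This stands as a limit on the size of the problem. It does not remove it: the amendment sets a rule for Regimen 1 patients still in the intensive phase, so entry was probably recent, and those patients cannot complete the regimen. It is therefore unlikely that 323 evaluable completers were already in hand. The amendment also does not expressly close allocation to Regimen 1, so a two-arm continuation is an inference. If allocation continued, later entrants still could not count towards 323 on moxifloxacin.
- *Concurrent controls are an analysis choice.* Correct; the plan does not impose that restriction. Both columns are shown for this reason. Both lie below 90% at every share short of 100%.
- *Over-recruitment is hypothetical.* A reader might infer that Regimens 2 and 3 will be over-enrolled to make up 1200. Nothing in the documents says that unfilled Regimen 1 places are reallocated or that 1200 is a fixed total. The per-regimen derivation points instead to about 400 in each remaining arm. No excess can be claimed.

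How patients switched off moxifloxacin are to be analysed is a separate and weighty question. It bears on this point in one respect: the number reached in Regimen 1 means little unless the plan says who is counted.

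**Conclusion.** The point holds for one comparison and for the overall total. The stated 323 evaluable patients and 90% power for Regimen 1 versus 3 are no longer what the design can deliver, and the three-regimen total has not been restated to say what is still to be recruited. The loss of power cannot be fixed from the documents. Under the assumed shares of 25% to 90% it ranges from serious (43% or 58% power, depending on the controls) to slight (87% or 88%). This rests on the plan's own inputs, a true difference of zero, and the amendments as shown; part of the supplement just ahead of the 2006 amendment's text was not available for this check. It is a failure to update the plan, not an arithmetic error, and it is worth correcting because the remedy is cheap.

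**What to change.** Amend the Sample size section together with the 2006 change to Regimen 1:

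1. State whether allocation to Regimen 1 is closed, and from what date.
2. If it is closed, replace the three-regimen total with a target of 323 evaluable (about 400 enrolled) in each of Regimens 2 and 3, that is 2 x 323/0.81 = 798, plus the patients already entered in Regimen 1. Do not keep 1200 as a fixed total.
3. Withdraw the 90% power statement for Regimen 1 versus 3. State the number reached and who is counted in it, and report that comparison as an estimate with its confidence interval, saying whether the controls are concurrent only or all of Regimen 3.
4. Keep the 90% power statement for Regimen 2 versus 3.

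The cost is one paragraph and no additional patients. The downside is that the stated power for the moxifloxacin comparison becomes less favourable.

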**Patients:**

Patients aged 18 years and above residing in or around Chennai or Madurai will be eligible for enrollment to the study. They should not have anti-TB treatment in the past or should have had less than one month of treatment (but less than one week in the preceding one month before enrollment in the study).

They should have sputum culture-positive pulmonary tuberculosis (at least two cultures should be positive). Patients will be enrolled to the study when two sputum smears are positive and will be retained for analysis only if two cultures are positive.

They should consent to attend the treatment centre for supervised treatment for 6 months and for home visits by the staff of the center.

They should give written informed consent.

The following patients will not be eligible for the study:

Those with

- body weight less than 30 kg
- hepatic or renal disease as evidenced by clinical or biochemical abnormalities
- diabetes mellitus
- a history of seizures
- psychiatric illness
- an abnormal electrocardiogram or those on anti-arrhythmic medication
- Those in a moribund state
- Those sero-positive for HIV antibodies
- Pregnant or lactating women

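### The inflation to 1200 has no term for the protocol's own two-positive-culture exclusion, and does not clearly cover loss during treatment

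*Supplement*

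**What the plan says.** The Sample size section of the protocol sets a control success rate of 95% in drug-susceptible disease, "taking into account both failures at the end of treatment and relapse over 24 months", with a margin of 5 percentage points. The error rates are "Type I error to be 5% (0.05, 1 tail) Z = 1.64" and "Type II error to be 10% (0.1) Z = 1.28". This gives 323 per regimen and 969 in all. Two allowances follow. One is for follow-up: "Loss in follow-up over 24 months is expected to be 10" per cent. The other is for drug resistance at intake, also 10%. The conclusion is "The required sample size for the trial will therefore be 969/ (0.9 x 0.9) = 1196 or approximately 1200 patients".

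The Patients section describes a two-step entry: "Patients will be enrolled to the study when two sputum smears are positive", but they remain in the analysis only if two cultures are positive. It gives no expected rate for this removal. No section says that removed patients are replaced, or that 1200 counts only culture-confirmed patients. The amendments shown do not alter the sample size.

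The Follow-up section, and the follow-up part of Clinical assessments and Investigations, place the 24 months after the end of treatment, making 28 to 30 months in total.

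**The concern.** An inflation for losses should cover every route by which an enrolled patient drops out of the analysed set. The culture rule is such a route, it is built into the design, and it acts after enrolment. The drug-resistance factor cannot stand in for it. Susceptibility tests are run on positive cultures, before and after the October 2005 amendment, so a patient with no positive culture cannot be counted as resistant.

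The second gap is less certain. If the 10% loss refers only to the 24 months after treatment, nothing is allowed for loss during the 4 to 6 treatment months. The protocol foresees such loss: Treatment Regimens provides for home visits to defaulters, and Ethical Considerations allows withdrawal at any time.

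At stake is whether planned enrolment supports the stated type II error of 10%. A reader weighing a conclusion of equivalence needs the number of patients who will actually be evaluable.

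**Working it through.** **Inputs from the Sample size section.** Success rate 0.95 in each regimen; margin 0.05; z = 1.64 and 1.28; three equal regimens; two loss factors of 0.9. The bracketed 0.01 beside each 10% is a slip with no effect, because the division uses 0.9.

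**Input not in the documents.** The share c of enrolled patients without two positive cultures. Values of 3%, 5% and 10% are assumed for illustration.

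**Step 1: reproduce the plan.**

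- Per regimen: 2 x 0.95 x 0.05 x (1.64 + 1.28)² / 0.05² = 324.0. The plan prints 323, a rounding difference.
- Total: 3 x 323 = 969.
- Inflated: 969 / (0.9 x 0.9) = 1196.3, taken as about 1200.

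The plan's arithmetic is sound for the two losses it names.

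**Step 2: slack at 1200.** 1200 x 0.9 x 0.9 / 3 = 324.0 evaluable per regimen. This equals what the formula requires, so there is no reserve for a third loss.

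**Step 3: add the culture exclusion.**

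- Evaluable per regimen: n = 324 x (1 − c).
- One-sided power, normal approximation: Φ(0.05 / √(2 x 0.0475 / n) − 1.645).

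For c = 5%: n = 324 x 0.95 = 307.8; the standard error is √(0.095 / 307.8) = 0.01757; 0.05 / 0.01757 = 2.846; 2.846 − 1.645 = 1.201; Φ(1.201) = 0.885.

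| Assumed exclusion c | Evaluable per regimen | One-sided power |
|---|---|---|
| 0% | 324 | 89.9% |
| 3% | 314 | 89.1% |
| 5% | 308 | 88.5% |
| 10% | 292 | 87.0% |

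**Step 4: where the shortfall begins to matter.** Power falls below 88% once the extra loss reaches about 6.8%, that is n = 324 x 0.932 = 302.

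**Step 5: treatment-phase loss.** If such loss also removed patients from the evaluable set, it would act as a further multiplier. A 5% culture exclusion with 5% treatment loss gives 324 x 0.95 x 0.95 = 292 and about 87.1%. This line depends on two things the documents do not settle: whether the 10% already includes the treatment months, and whether defaulters leave the denominator.

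**The case against.** The best reply is that the division is correct and that only an unstated assumption is at issue. That is fair: this is an omission, not a miscalculation.

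The culture exclusion may also be small. Patients enter with two positive smears and little or no previous treatment, and at least four baseline specimens are cultured, of which two must be positive. This favours a low rate but does not supply one. Two positive cultures is also listed as an eligibility condition, so 1200 could be read as culture-confirmed patients. The Sample size section does not say so, and one sentence would settle it.

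On treatment-phase loss the objection largely succeeds. The follow-up sections support reading the 24 months as post-treatment, but the Sample size section does not say that the 10% leaves out earlier loss. Defaulters might be counted as unfavourable, in which case the evaluable number would not fall. No analysis plan is shown, so their handling cannot be called missing. Observed dosing and home visits should also limit such loss. What stands is a request for clarity.

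A reader might infer three stronger conclusions, none of which the documents support:

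- That 90% power is definitely not delivered. Without a rate this cannot be said, and up to nearly 7% extra loss the shortfall is within about 2 points.
- That exclusion of about 0.3%, enough to pass from 324 to 323, is a meaningful threshold. It arises from rounding; power is 89.9% at 324 and 89.8% at 323.
- That power drops into the 70s because the section opens with "Applying an equivalence design and". Requiring both bounds gives about 80% at 324 per regimen before any exclusion. That gap concerns sidedness, a separate question, and the section specifies one tail.

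**Conclusion.** The point holds in a limited form. The enrolment target omits a loss that the protocol itself imposes and leaves no room for it. If the culture exclusion is appreciable, fewer than the stated number will be evaluable and one-sided power will be somewhat below 90%: about 89% to 87% for exclusions of 3% to 10%. Coverage of treatment-phase loss is unclear rather than shown to be absent.

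These figures assume 95% success in each regimen, 400 enrolled per regimen, both planned losses occurring at exactly 10%, and independent losses that multiply. The equal split follows the Sample size section. The November 2006 change to Regimen 1 did not restate it, and its effect on that comparison is outside this point.

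**What to change.** Amend the Sample size section in one of two ways:

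1. State that 1200 counts culture-confirmed patients. The present inflation then stands on this point.
2. Otherwise, add a factor (1 − c) for culture exclusion, with c taken from the pooled, arm-blind rate in patients enrolled so far. Report the evaluable number per regimen as 1200 x 0.81 x (1 − c) / 3, with the matching one-sided power.

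In either case, say whether the 10% loss includes the treatment months or only the 24 months after them.

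The cost is a few restated lines and possibly a slightly less favourable power figure. No extra enrolment is proposed, and nothing in patient management changes.

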**Study Progress Review Panel:**

A Panel consisting of three doctors, a bacteriologist and a statistician will review:

- all cases at the end of treatment after the sputum smear results are available,
- all cases with sputum cultures resistant to rifampicin and isoniazid,
- change of treatment on clinical/ or radiological deterioration,
- bacteriological relapse,
- at any other time if considered necessary by the doctors.

Patients will be prescribed calcium lactate one tablet daily after treatment phase till the end of follow-up

**Outcome measures:**

The following outcome measures will be compared between regimens:

a) Sputum culture conversion at 2 months of treatment,

b) Favourable bacteriological response at end of treatment

c) Unfavourable bacteriological response at end of treatment

d) Doubtful bacteriological response at end of treatment

e) Relapse after successful treatment.

f) Adverse reactions to anti-TB drugs, especially to moxifloxacin and gatifloxacin.

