**Definition of Outcome Measures:**

*Sputum culture conversion at 2 months*: The proportion of patients with negative sputum cultures at 2 months of treatment.

*Favourable bacteriological response at end of treatment:*

A patient will be classified as having had a 'Favourable' bacteriological response at end of treatment if all three cultures are negative in the last month of treatment.

*Unfavourable bacteriological response:*

A patient will be classified as having had an 'Unfavourable' bacteriological response at end of treatment if more than one culture is positive in the last month of treatment, one of which is at least 20 colonies or more.

*Doubtful bacteriological response:*

A patient will be classified as having had a 'Doubtful' bacteriological response if one or more cultures are positive in the last month of treatment, none of which is 20 colonies or more.

The physicians acting in consultation can decide on a change of treatment based on clinical and/or radiological deterioration and persistent sputum positivity. Such cases will be put up to the Panel for ratification of the decision.

*Relapse after treatment:*

In patients who have had a favourable or doubtful bacteriological response at the end of treatment, relapse during follow-up is defined as either I) two positive sputum cultures in a 2-month period, one of which is at least 20 colonies, (such patients will be retreated if at least one sputum smear is also positive)

or ii) positive sputum cultures during four consecutive monthly examinations, one of which is at least 20 colonies.

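### The trial is sized on a combined failure-or-relapse outcome, but the outcome list omits it, names no primary, and compares failure and relapse separately

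*Supplement*

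**What the plan says.** **Sample size.** The calculation is built on one quantity, "assuming that the efficacy of the control regimen (Regimen 3) will be 95% (0.95) in patients with drug susceptible disease", and that efficacy is reached by "taking into account both failures at the end of treatment and relapse over 24 months". Error rates are given as "Type I error to be 5% (0.05, 1 tail) Z = 1.64" and "Type II error to be 10% (0.1) Z = 1.28". One margin of 5 points is stated, here and nowhere else. The result is "Sample size for 3 regimens = 3 x 323 = 969", raised to about 1200 for 10% loss to follow-up and 10% drug resistance at intake.

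**Outcome measures.** Six items are to be compared between regimens: (a) 2-month culture conversion; (b), (c) and (d) favourable, unfavourable and doubtful response at end of treatment; "e) Relapse after successful treatment"; and (f) adverse reactions. None is called primary, and none combines failure with relapse.

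**Definition of Outcome Measures.** No combined outcome is defined. The relapse definition opens "In patients who have had a favourable or doubtful bacteriological response at the end of treatment, relapse during follow-up is defined as either", so patients with an unfavourable response are outside it.

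**Background.** The closing statement of aims has the same separated form: conversion at 2 months, results at end of treatment, relapse rates.

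**Amendments.** The October 2005 amendment changes an eligibility criterion, dose counts, the doubtful category, susceptibility testing and laboratory monitoring. The later amendment, following the October and November 2006 reviews, changes treatment in regimen 1. Neither adds a combined outcome or names a primary one.

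**The concern.** An equivalence trial is decided by one comparison against one margin. Here the margin belongs to an outcome that is not on the list of things to be compared, and the listed outcomes have no margin.

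Two consequences follow. First, failure and relapse compete for the same 5 points. A shorter regimen can be less than 5 points worse on each and still more than 5 points worse in total. Second, relapse among non-failures does not compare the groups as randomised. An arm with more failures removes those patients from its relapse denominator, so its relapse rate may look better than the regimen deserves. Relapse is the natural cost of shortening treatment from 6 to 4 months, so this component carries much of the trial's question.

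Without a named deciding outcome, the choice between a combined and a component-wise comparison could be made after the results are known.

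**Working it through.** **1. The plan's own figure.** Inputs from the Sample size section: p = 0.95, Z = 1.64 and 1.28, margin 0.05.

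n = 2 × 0.95 × 0.05 × (1.64 + 1.28)² / 0.05² = 0.095 × 8.5264 / 0.0025 = 324.0 per arm (plan: 323).

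3 × 323 = 969, and 969 / (0.9 × 0.9) = 1196 (plan: 1196, about 1200).

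The figure reproduces for the combined outcome. The 323 is the number left after losses and resistant cases are removed.

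**2. How two components add up.** With failure probability f and relapse probability r among non-failures, the combined unfavourable rate is f + (1 − f)r. The documents do not split the control arm's 5%. As an illustration, take f = 0.02 and r = 0.0306:

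- Control: 0.02 + 0.98 × 0.0306 = 0.050.
- Test, 3.5 points worse on each: 0.055 + 0.945 × 0.0656 = 0.117.
- Combined difference: 0.117 − 0.050 = 0.067.

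Each component is inside 5 points, yet the total is 6.7 points worse.

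**3. False equivalence at a true combined deficit of 5 points (5% v 10%).** The following are assumptions, not plan content:

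- the 5-point margin is applied to failure and again to relapse among non-failures, and both must pass;
- control failure is 1% or 2%, with relapse making up the rest of the 5%.

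Simulation: 500,000 trials per scenario, 323 per arm, upper limit = difference + 1.645 × unpooled standard error, passing if below 0.05. The excess is split in percentage points of all patients.

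| Excess on failure / relapse (points) | Both components pass | Combined test passes |
|---|---|---|
| 0 / 5 | about 5% | about 5.5% |
| 0.5 / 4.5 | 8% | about 5.5% |
| 1 / 4 | 13% | about 5.5% |
| 2 / 3 | 22–23% | about 5.5% |
| 2.5 / 2.5 | 24–26% | about 5.5% |
| 5 / 0 | about 6% | about 5.5% |

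**4. Power of the combined test.** With 5% unfavourable in both arms and 323 per arm, it passes 89–90% of the time, as planned.

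**5. Why the denominator matters.** 323 / 0.9 = 359 drug-susceptible patients per arm before losses. If all 359 are analysed and the 10% lost are counted as not unfavourable, the false equivalence rate at a true 5-point deficit rises to about 9%. If they are counted as unfavourable, power with no true difference falls to about 60%. Analysing the assessable patients keeps about 5.5% and 89–90%, provided losses are unrelated to outcome.

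**The case against.** The strongest reply is that any inflation belongs to a decision rule the protocol does not contain. It states one margin, attaches it to the combined efficacy, and elsewhere says only that the measures will be compared. No separate analysis plan is shown, and a decision rule may properly sit in one. This stands: a reader might infer that the plan carries a false-claim rate near 25%, and the documents do not support that.

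A second reply is that the combined count is easily obtained. Unfavourable response and relapse are both defined and ascertained, and they add up. This also stands. A reader might infer that the trial cannot estimate the quantity it was sized for, which would be too strong. The data will be there, but nothing commits the trial to forming the sum or testing it against the margin.

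A third reply is that the near-equal split is close to the worst case. The Background cites a 4-month ofloxacin regimen with 99% cure at end of treatment and relapse below 5%, which suggests that failure is the smaller component. That favours the lower rows of the range, 5% to 13%, though it says nothing certain about these regimens.

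None of these replies removes the mismatch. Naming the outcome on which the trial is sized belongs in the protocol, and its outcome list conflicts with its own sample-size section.

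**Conclusion.** The concern holds as an inconsistency within the protocol. The sized outcome is neither listed nor defined, no outcome is primary, and the listed relapse comparison uses a group selected after randomisation. No amendment mends this.

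The effect on error is conditional. If 5 points were allowed on each component and both had to pass, the false equivalence rate at a true 5-point combined deficit would run from about 5% to 26%, depending on how the excess divides. The combined test gives about 5.5%. These figures assume control failure of 1–2%, 323 assessable patients per arm and a one-sided 5% Wald limit. When nearly all the excess lies on one component there is no material inflation. A looser rule, under which either component alone suffices, would give much higher rates, but nothing in the documents points to it and the conclusion does not rest on it.

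**What to change.** Add a new item to Outcome measures and name it primary: unfavourable status, meaning an unfavourable bacteriological response at end of treatment or relapse within 24 months after it. Compare it by allocated regimen in patients with culture-positive, drug-susceptible disease at baseline. Test it against the 5-point margin with the one-sided 95% limit implied by the Sample size section. Make (a) to (e) secondary. Relapse is still reported, described as conditional on response.

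The same amendment should settle three matters:

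- **Losses.** Keep the main denominator consistent with the Sample size section, which takes 323 per arm as assessable after losses. Add sensitivity analyses that count patients lost to follow-up in different ways, because either extreme distorts the result (step 5 of the working).
- **Treatment changes.** State how patients whose treatment was changed for deterioration or persistent positivity, as Definition of Outcome Measures allows, are classified in the primary outcome.
- **Regimen 1.** Report separately the patients whose treatment was modified under the amendment that ended moxifloxacin, so that they do not pull that arm towards control. The documents do not say how many they are, so regimen 1's remaining power cannot be judged here.

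The cost is a short amendment and a few more analyses, with no new data or patients. At 323 assessable per arm, power stays at about 89–90% with no true difference.
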